## Methods/design

### Aims

The aims of this RCT are to test the outcomes of the **HF**-FamPAL**home**CARE bundled intervention, with patients and family caregivers (104 dyads) managing home supportive EOLPC for end-stage HF in rural WV. The specific aims and hypotheses, with outcome measures for this RCT, are listed in Table 1.

**Table 1 Tab1:** Specific Aims, Hypotheses, with the Outcome Measures for this RCT

**Primary Aims** are to test the outcomes of the **HF**-FamPAL**home**CARE bundled intervention, with patients and family caregivers managing home supportive EOLPC for end-stage HF in rural WV
**Aim 1:** Compared to the control group at 3, 6, 9 months, and 1-year follow-up:
***Hypothesis 1a.*** The patients in the intervention group will have higher scores on HF-related health quality-of-life measure and on the functional health well-being scale
***Hypothesis 1b.*** The family caregivers in the intervention group will have higher scores on the functional health well-being scale
**Aim 2:** Compared to the control group at 3, 6, 9 months, and 1-year follow-up:
***Hypothesis 2a.*** The patients in the intervention group will have (a) lower depression and anxiety scores and (b) higher numbers of signed EOL advance directives
***Hypothesis 2b.*** The family caregivers in the intervention group will have (a) lower depression and anxiety scores, (b) lower home caregiving burden scores, and (c) improved home HF EOLPC preparedness and improved home palliative care scores
**Secondary Aim** (Aim 3) is to assess the bundled intervention helpfulness, cost, and the plans for maintaining the sustainability of our faith community nurses and visiting volunteers engagement across rural WV
***Aim 3a.*** Compare the bundled intervention helpfulness questionnaire ratings by the patient, family caregiver intervention group participants, and the interventionists (faith community nurse and visiting volunteers). Determine the implementation cost of the **HF**-FamPAL**home**CARE bundle
***Aim 3b.*** Using focus group research, determine 10-year plans for sustaining the bundle implementation, maintaining rural volunteers and coordinating administrative aspects of the program

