#### Sample size

The power and sample size determination is based on a preliminary RCT, which revealed a moderate effect reduction in the burden of caregiving and improvements in patients’ HF-related health status [15]. With the use of G*Power v.3.1.9.7 for repeated-measures ANOVA with α = 0.05, Cohen’s d = 0.25 (moderate effect size), a power of 80%, two groups with 5 measurements, and correlations among repeated measures (0.50), a *sample size of 86 family dyads* will be needed. Our power analyses performed by this study’s statistician indicate that this sample size is sensitive enough to detect a significant difference in the study outcomes with this repeated measure design [36].

Our biostatistician’s revised precision calculation for linear mixed model analysis was based on the effect size outcomes of our HF palliative care studies. To account for an expected 20% attrition (many due to HF-related deaths), eight additional families will be recruited for each group. The calculated sample size was 86 patients, with an additional n = 18 for the expected 20% attrition rate (total sample N = 208; 104 patients and 104 caregivers) for this study. In this analysis, the random and fixed effects and quarterly repeated measures also add power.

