### Data analyses

All the outcome measures have established discriminant or construct validity, internal consistency, reliability, and specificity. Each has been used with diverse populations, chronic illness patients, and HF families. These measures have been shown to distinguish clinically significant differences and are responsive to changes over time. These questionnaires were easily completed within 30 min. The sample demographics will be tabulated and reported.

#### Data analysis for Aims 1 & 2

Our experienced statistician will employ hierarchical generalized linear models with repeated measures to identify significant differences in outcomes between groups and to control for nested dyadic analysis [49]. The models will include fixed effects of treatment, time, and the treatment‒time interaction. Patient and family caregiver effects will be treated as random to account for dependence among repeated observations on the same subject as well as among subjects within the same family [37]. These models detect changes in outcome variables over time, differences between groups, and within-group differences over time. The SAS Proc MIXED procedure will be utilized. General linear modeling using linear contrasts of selected model parameters will test for significant differences. Point estimates and confidence intervals will be produced via contrasts and estimates of appropriate linear combinations of model parameters. The overall experimental error rate will be controlled via the Bonferroni procedure for multiple testing.

Multicollinearity among study variables will be determined and statistically controlled for in the data analysis. The number of mental health visits (for severe anxiety and depression) will be tracked for comparison between groups. To assess differences in HF EOLPC decisions, the number of family members and patients who sign an advance directive form, reveal a decision, or identify someone to help with HF EOLPC options will be recorded and reported. The proportion of patients signing an advance directive form will be used to evaluate the acceptability of EOLPC discussions. Subjects’ outcomes will be recorded at the time of death or 12 months postintervention, whichever comes first.

#### Data Analysis for Aim 3

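### Aims 1 and 2 name no deciding outcome, visit, contrast or all/any rule, and the sample size assumes an alpha that the planned Bonferroni control does not leave

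*Protocol article*

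**What the plan says.** Table 1 (Aims) labels Aims 1 and 2 as primary and opens each with "Compared to the control group at 3, 6, 9 months, and 1-year follow-up". The hypotheses beneath list five patient outcomes (HF quality of life, functional well-being, depression, anxiety, signed advance directives) and six caregiver outcomes (functional well-being, depression, anxiety, burden, preparedness, home palliative care). Outcomes are joined within a hypothesis. Hypothesis 1a, for example, reads "The patients in the intervention group will have higher scores on HF-related health quality-of-life measure and on the functional health well-being scale".

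The section on data analysis for Aims 1 and 2 specifies a mixed model with treatment, time and their interaction as fixed effects. It says "These models detect changes in outcome variables over time, differences between groups, and within-group differences over time", and then "General linear modeling using linear contrasts of selected model parameters will test for significant differences". Those parameters are not identified. The same paragraph assigns the error rate for the experiment as a whole to Bonferroni, without giving the family or the number of tests.

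The Sample size section cites a preliminary trial that showed "a moderate effect reduction in the burden of caregiving" and better HF-related health status in patients. It uses "repeated-measures ANOVA with α = 0.05", an effect of 0.25 labelled both Cohen's d and "moderate effect size", "a power of 80%, two groups with 5 measurements", and a correlation of 0.50. The result is 86 dyads, raised to 104 for attrition.

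**The concern.** A primary hypothesis needs a rule for what result supports it. Here one outcome can be judged by the difference at any of four visits, by a difference averaged over visits, or by the interaction. These answer different questions. Averaged over all five measurements, the treatment effect takes in baseline, where randomisation makes the expected difference zero. The interaction responds to any difference in the shape of the two curves. A visit contrast looks at one time only. Joining visits and outcomes without an all/any rule adds a second open choice.

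The error control and the sample size also do not fit together. If Bonferroni covers the whole set of primary comparisons, each test runs far below 0.05, yet the 86 dyads were computed at 0.05. What is at stake is whether the trial can state in advance what counts as success, and whether it has a reasonable chance of reaching it.

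**Working it through.** **1. The plan's own figure.** Using the noncentral F with G*Power's parameterisation, m = 5, ρ = 0.5, alpha 0.05 and power 80%:
- Between-groups test, λ = N·f²·m/(1+(m−1)ρ): N = 78 for f = 0.25, and 304 for f = 0.125 (a literal d = 0.25, since f = d/2 for two groups).
- Interaction test, λ = N·f²·m/(1−ρ): N = 22 for f = 0.25, and 78 for f = 0.125.

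None of these gives 86, so the sample size does not reveal which test was meant to decide. At N = 86 with f = 0.25, the between-groups test has 84% power at 0.05, 53% at 0.05/11 = 0.0045, and 36% at 0.05/44 = 0.0011.

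**2. The size of the family.** Five patient plus six caregiver outcomes make 11; times 4 visits, 44 comparisons.

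**3. Does Bonferroni hold the error rate?** I simulated 100,000 sets of 11 × 4 correlated normal statistics, with correlation 0.5 between visits and 0.5 between outcomes. Bonferroni over all 44 gives a family-wise error of about 0.04. It does hold.

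**4. Power of the candidate contrasts for one continuous outcome.** From the Sample size section: 86 dyads, taken as 43 per arm, and correlation 0.5. Assumed: equal correlation between all visits, SD 1, complete data, two-sided tests, and a constant effect δ after baseline. Power is from the noncentral t with 84 df and noncentrality δ/SE; normal approximation or simulation moves it by at most about 3 points.
- Single visit (the raw difference and the change from baseline both have SD 1, because 2(1−0.5) = 1): SE = √(2/43) = 0.216.
- Five-visit main effect: the effect shrinks to 4/5 of δ; variance (1+4×0.5)/5 = 0.6; SE = √(0.6×2/43) = 0.167.
- Baseline-adjusted follow-up average: variance (1+3×0.5)/4 − 0.5² = 0.625 − 0.25 = 0.375; SE = √(0.375×2/43) = 0.132.

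| Contrast | Alpha | δ = 0.5 SD | δ = 0.25 SD |
|---|---|---|---|
| Single visit | 0.05 | 63% | 21% |
| Single visit | 0.05/44 | 16% | 2% |
| Five-visit main effect | 0.05 | 66% | 22% |
| Follow-up average, baseline-adjusted | 0.05 | 96% | 46% |
| Follow-up average, baseline-adjusted | 0.025 | 93% | 35% |
| Follow-up average, baseline-adjusted | 0.05/11 | 80% | 16% |

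Both values of δ are shown because 0.25 is a moderate effect as f (equivalent to d = 0.5), while the text calls it d.

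**5. All or any.** In simulation (20,000 trials, δ = 0.5 SD, change from baseline, unadjusted 0.05), all four visits are significant in 32% of trials and at least one in 90%. At 0.05/44 the figures are 2% and 38%. The chance of success on one outcome therefore depends on a rule that the plan does not state.

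**6. How much is the baseline adjustment alone?** A baseline-adjusted single visit has SD √0.75 and power 75% at 0.05 and 25% at 0.05/44 (δ = 0.5 SD). Most of the gain comes from averaging the visits and from needing one test per outcome instead of four.

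**The case against.** The documents narrow the choice more than a quick reading suggests. The hypotheses are all against control and at named visits, so the natural reading is between-group contrasts at those visits; within-group change is something the model describes, not a rival test. Exact contrasts and the Bonferroni family are also often left to a statistical analysis plan, which is not shown. Both points have force. However, the natural reading still leaves four visits, about 11 outcomes and no all/any rule. The rule for success belongs with the primary hypotheses, which this document does state.

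Four stronger readings are tempting, and the text does not support them:
- **Inflated false positives.** Bonferroni only within each outcome's model, or only across outcomes, would give family-wise errors of about 0.29 or 0.13. The plan speaks of the error rate of the whole experiment, and on that plain reading the figure is about 0.04.
- **Every type of test is run and all are joined.** Main effect and interaction appear as model terms; the only test stated is by contrasts. The joining in Table 1 is of outcomes and visits, not of types of test.
- **The same data could both support and refute the bundle.** A non-significant result does not refute it. With each candidate at roughly 63% to 67% power, disagreement between tests is partly ordinary low power.
- **Power is reserved for burden and patient health status.** The Sample size section cites them as the source of an effect size and then refers to the study outcomes in general.

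On effect size, the objection that 0.5 SD doubles the stated d is fair, which is why both columns are given. The normal-theory figures do not apply to signed advance directives, which is a count or proportion.

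**Conclusion.** The concern holds in this form: no outcome, visit, contrast or all/any rule is named as deciding Aims 1 and 2, and the sample size at alpha 0.05 does not match the stated multiplicity control. The harm is an open choice of contrast and a large loss of power, not excess false positives.

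Under the assumptions listed, and an effect of 0.5 SD, a visit-specific test falls from 63% to 16% power once all 44 comparisons share the error rate. One baseline-adjusted average per outcome keeps 80% at 0.05/11. If the effect is 0.25 SD, the average is still clearly better than a single visit, but no candidate reaches 50% even at unadjusted 0.05.

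The figures rest on a constant effect after baseline; an effect that grows or fades would shrink the advantage of the average over the best single visit. They also assume 86 complete dyads, slightly more than 104 × 0.8 = 83.2.

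**What to change.** In the data analysis section for Aims 1 and 2:
- Replace the unspecified contrasts with one deciding contrast per outcome: the between-group difference averaged over 3, 6, 9 and 12 months, adjusted for baseline. For signed advance directives, state a matching contrast suited to a binary outcome.
- State, there and in Table 1, that each outcome is judged on its own.
- Define the multiplicity family as one test per primary outcome, and use Holm in place of Bonferroni. The 0.05/11 power is then a floor, because only Holm's first step is that strict.
- Report the interaction, visit-specific differences and within-group changes as estimates with confidence intervals.

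In the Sample size section, say which test is powered and whether 0.25 is d or f, and restate power at the resulting alpha. Making patient HF-related quality of life and caregiver burden the only two deciding outcomes (alpha 0.025 each at Holm's first step, 93% power at 0.5 SD) is an option for the sponsor, not a requirement.

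The cost is a few sentences, settled before unblinding and carried into the registry entry, with no extra participants or data. The downside is that single-visit differences can no longer be headline claims.

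### The 80% power claim uses an unadjusted alpha of 0.05, while the analysis controls the overall error rate by Bonferroni across 9 to 11 outcomes under the primary aims

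*Protocol article*

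**What the plan says.** Three parts of the protocol article bear on this.

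- **Sample size.** The calculation is "for repeated-measures ANOVA with α = 0.05", 80% power, "two groups with 5 measurements" and a correlation of 0.50. The effect size is given as Cohen's "d = 0.25 (moderate effect size"). The result is a "sample size of 86 family dyads", raised to 104 for 20% attrition. The section says this size is sensitive enough for the study outcomes in general. It also mentions a revised calculation for the linear mixed model, but gives no alpha or effect size for it and arrives at the same 86.
- **Aims, Table 1.** Aims 1 and 2 both stand under the primary aims, and each is introduced with "Compared to the control group at 3, 6, 9 months, and 1-year follow-up". No outcome or visit is singled out as primary.
- **Data analysis for Aims 1 & 2.** "The overall experimental error rate will be controlled via the Bonferroni procedure for multiple testing". The section does not say how many tests the procedure covers. It says that linear contrasts of selected model parameters will be tested, without naming them.

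**The concern.** An unadjusted 0.05 and Bonferroni control of the overall error rate cannot both apply to the same set of tests. The sample size supports the first; the trial will be judged by the second. This is a conflict between two choices that the article states, not a detail left for an unseen analysis plan. A plan could define the family, but at 86 dyads any family of two or more tests takes power below the stated 80%.

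At stake is how a negative result is read. If an effect of the planned size exists and misses the adjusted threshold, readers who rely on the 80% claim may take the miss as evidence of no benefit.

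**Working it through.** **Number of tests.** From Table 1: hypothesis 1a has 2 outcomes, 1b has 1, 2a has 3 and 2b has 5, so 2 + 1 + 3 + 5 = 11. If depression and anxiety form one score per person, the count is 2 + 1 + 2 + 4 = 9. Testing 11 outcomes at each of four visits would make 44.

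**Reproducing 86.** For the between-groups test, λ = N f² m / (1 + (m − 1)ρ), with 1 and N − 2 degrees of freedom. With f = 0.25, m = 5 and ρ = 0.50, λ = N × 0.0625 × 5 / 3 = 0.1042 N. The smallest even N with 80% power at 0.05 is 78, not 86. At N = 86, λ = 8.96 and power is 84%.

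Other readings:
- Between-groups, f = 0.25, three measurements: exactly 86, but the text says five.
- Group-by-time interaction, f = 0.25: 22.
- Group-by-time interaction, f = 0.125: 78 (82 to 84 in MANOVA form).
- Between-groups, literal d = 0.25 (f = 0.125): 304. With 86 dyads λ = 2.24, and power is 32% even at 0.05.

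I take 0.25 as f, because 0.25 is the conventional moderate value of f and the text calls it moderate. This is an assumption.

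**Power per outcome under Bonferroni.** Same formula with alpha = 0.05/k. The 83 dyads are 104 × 0.8 = 83.2.

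| Tests k | Alpha | 86 dyads | 83 dyads |
|---|---|---|---|
| 1 | 0.05 | 84% | 83% |
| 2 | 0.025 | 76% | 74% |
| 4 | 0.0125 | 67% | 65% |
| 9 | 0.0056 | 56% | 54% |
| 11 | 0.0045 | 53% | 51% |

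The other variants that give an N near 86 agree. At k = 2, power with 86 dyads is 71% (three measurements), 77% (interaction, f = 0.125) or 74% (MANOVA form). At k = 11 it is 47%, 56% or 51%.

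**If each visit is tested separately.** The test then uses one visit, not the average of five. In units of the outcome SD, λ = N d² / (4σ²), with d = 0.5.
- Unadjusted, σ² = 1: λ = 86 × 0.25 / 4 = 5.375. Power is 63% at 0.05 and about 16% at 0.05/44 = 0.0011.
- Baseline-adjusted at r = 0.5, σ² = 1 − 0.25 = 0.75: λ = 7.17. Power is about 25% at 0.05/44.

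**One baseline-adjusted contrast per outcome.** The mean of four follow-up visits has variance (1 + 3 × 0.5)/4 = 0.625. Baseline adjustment removes 0.5² = 0.25, which leaves 0.375. With 86 dyads, λ = 86 × 0.25 / (4 × 0.375) = 14.33. Power is about 80% at 0.05/11 (78% with 83 dyads) and about 93% at 0.05/2 (92% with 83). Without baseline adjustment the variance stays at 0.625 and power at 0.05/11 is 51%, so the gain comes from the adjustment.

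**A single 12-month contrast at 0.025.** Unadjusted 52% and adjusted 65% with 86 dyads; 50% and 64% with 83.

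**The case against.** The strongest objection is that the article never defines the Bonferroni family. It might cover visits within an outcome, outcomes, or both, and a condensed article may leave that to the full protocol or analysis plan. This stands, and it limits what can be claimed. A reader might infer that the plan commits to 44 tests and that no outcome carries an alpha of 0.05. The article does not say so; 44 is one reading among several.

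A reader might also put 0.05/44 into the five-measurement formula and get 36% power with 86 dyads, or a need for 168 dyads. Those figures describe no coherent test: the alpha belongs to visit-specific tests and the power to an average over all five measurements.

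Three further points have some force.

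- The contrast is not fixed either. On a baseline-adjusted mean of months 3 to 12, power at 0.05/11 is already about 80%, so 53% is not inevitable. But the Sample size section does not base its claim on that contrast.
- The mixed-model recalculation may have used other inputs. None is given, so it cannot support the claim.
- All 104 enrolled dyads would do better. With no attrition they keep 80% for up to three tests (80.3%), but give 77% for four and 65% for eleven. The protocol itself expects 20% attrition.

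**Conclusion.** The point holds in this form: the stated 80% power is for a single test at 0.05 and does not describe power under the plan's Bonferroni rule. Under the plan's own ANOVA, with 0.25 read as f, five measurements and a correlation of 0.50, power per outcome with 86 dyads falls from 84% to 76% for two tests and to 53 to 56% for nine to eleven. Every variant that yields an N near 86 drops below 80% at two tests, so the conclusion does not depend on the exact count.

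The size of the loss does depend on the family and the contrast, and the figures are scenarios. It does not follow that the trial will more likely than not miss a real effect: with outcomes alone counted the chance is about even, and with a better contrast it is good. Two limits remain. If 0.25 really is d, power is 32% before any adjustment, which is a separate problem with the sample size statement. And the ANOVA calculation does not cover signed advance directives, which is a binary outcome.

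**What to change.** **Needed.** In Data analysis for Aims 1 & 2, state which tests the multiplicity procedure covers and which contrast is tested for each outcome. In Sample size, restate power at the resulting alpha, say whether 0.25 is d or f, give inputs that reproduce the N, and treat the advance-directive outcome separately. The cost is wording and one recalculation.

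**Recommended.** Replace Bonferroni with Holm, which controls the same overall error rate and is never less powerful. Test each continuous outcome once, on the baseline-adjusted mean of months 3 to 12, and report the separate visits as estimates with intervals. Under the stated assumptions, with d = 0.5 at each follow-up visit, this reaches about 80% at 0.05/11 with 86 dyads and needs no extra recruitment. The cost is that Table 1 must be reworded, and an effect present at only one visit would be diluted.

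**Optional, for the sponsor.** Name patient HF-related health status and caregiver burden, the two outcomes that the sample size rests on, as the primary pair. The other Table 1 outcomes then become secondary, which changes the stated aims. On the plan's ANOVA a pair at 0.025 still has only 74 to 76% power; on the baseline-adjusted mean it has about 92 to 93%. A single 12-month contrast should not be used for the pair without stating its lower power, about 50 to 65% at 0.025.

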#### Randomization

The consulting statistician will use computerized randomization to generate numbers for subject enrollment. Two separate randomization lists will be created: one for males and one for females. Families will then be randomly assigned to either the control or intervention group at a 1:1 ratio. The group assignments are placed in sealed envelopes according to sex. Our RCT design adheres to CONSORT standards and rigorous research procedures [30]. The study is designed to enhance both internal and external validity, making it suitable for detecting differences between groups in behavioral intervention trials [31].

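### Plain Bonferroni is valid here, but Holm's step-down test gives the same familywise control on the same p-values with equal or better power, so naming Holm would be a cheap improvement

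*Protocol article*

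**What the plan says.** The multiplicity rule stands under Data analysis for Aims 1 & 2: "The overall experimental error rate will be controlled via the Bonferroni procedure for multiple testing". No step-down version, testing order or single primary outcome is named. The sentence before it promises point estimates and confidence intervals from model contrasts, without saying whether the intervals are adjusted.

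Table 1 lists the hypotheses under the primary aims. Each aim is tested "Compared to the control group at 3, 6, 9 months, and 1-year follow-up". Hypothesis 1a alone predicts "higher scores on HF-related health quality-of-life measure and on the functional health well-being scale" for patients. The later hypotheses add caregiver functional well-being, depression and anxiety in both members of the dyad, advance directives, and caregiver burden, preparedness and palliative care scores.

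The Sample size section uses "repeated-measures ANOVA with α = 0.05" and gives the effect as "d = 0.25 (moderate effect size".

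**The concern.** Single-step Bonferroni compares every p-value with alpha/K. Holm does so only for the smallest p-value and relaxes the threshold at each further rejection. Any additional rejections that Holm makes are lost under Bonferroni, although the error guarantee is the same. The loss is greatest when many effects are real, and Table 1 predicts benefit on every listed outcome. What is at stake is how many of those hypotheses can be supported with about 42 dyads per arm at the end. The validity of the error control is not in question.

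**Working it through.** **Inputs**
- Familywise level 0.05, two-sided. The article gives 0.05 only under Sample size; taking it as the familywise level is an assumption.
- Number of outcomes, counted from Table 1: 2 (hypothesis 1a) + 1 (1b) + 2 to 3 (2a) + 4 to 5 (2b) = 9 to 11. The range depends on whether depression and anxiety are one score or two. With four follow-up times, 11 × 4 = 44 tests.
- Completers per arm: 104 dyads, allocated 1:1, less 20% attrition: 104 × 0.8 / 2 = 41.6, taken as 42.
- Effect size, three readings. (i) d = 0.25 as printed. (ii) d = 0.5, if 0.25 is really Cohen's f, for which 0.25 is the conventional medium value (two equal groups: d = 2f). (iii) d = 0.65, which is 0.5 SD expressed on the mean of five visits with correlation 0.5: 0.5 / √((1 + 4 × 0.5)/5) = 0.5 / 0.775 = 0.65.
- Correlation between test statistics 0.4 (assumption; the article gives none).

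**The plan's own figure.** The 86 dyads are not reproduced exactly. The between-groups repeated-measures F test with f = 0.25, five measurements and correlation 0.5 needs 78 for 80% power. At 86 its noncentrality is 0.25² × 86 × 5 / (1 + 4 × 0.5) = 8.96 (√8.96 = 2.99) and its power is 84% at alpha 0.05. At the Bonferroni level for 11 tests (0.05/11 = 0.0045) the power of that single test is 53%. The mismatch with 86 does not affect the present point.

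**Why Holm cannot do worse.** Order the p-values. Holm compares the i-th smallest with 0.05/(K − i + 1) and stops at the first failure. The first threshold equals Bonferroni's 0.05/K and every later one is larger, so every Bonferroni rejection is also a Holm rejection. For error control, let m₀ hypotheses be truly null. If any is rejected, the first one falls at step K − m₀ + 1 or earlier, so its p-value is at most 0.05/m₀. By the Bonferroni inequality the probability of that is at most m₀ × 0.05/m₀ = 0.05, whatever the dependence.

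**Size of the gain.** Single-test noncentrality is d√(42/2): 1.15, 2.29 and 2.98 for the three readings. Both rules were applied to the same simulated two-sided p-values (normal approximation, equal true effects). Mean power per real effect, Bonferroni to Holm:

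| Tests | Real effects | d = 0.25 | d = 0.5 | d = 0.65 |
|---|---|---|---|---|
| 11 | 11 | 4.5% to 5.1% | 29% to 36% | 56% to 68% |
| 11 | 5 | under 1 point | about 2 points | about 3 points |
| 11 | 2 | under 1 point | under 1 point | under 1 point |
| 44 | 44 | under 1 point | 17% to 20% | 39% to 48% |
| 44 | 22 | under 1 point | about 1 point | about 3 points |

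The Bonferroni entries can be checked by hand. With 11 tests the critical value is 2.84, so power at d = 0.5 is Φ(2.29 − 2.84) = Φ(−0.55) = 29%. In no run did Holm miss a Bonferroni rejection. With all nulls true, the familywise error was about 4% under both rules. The chance of at least one detection hardly moves: with 11 tests, all real, at d = 0.5 it is 81.1% under both.

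**The case against.** The strongest reply is that nothing here is wrong. The article promises control of the overall error rate, and Bonferroni delivers it. That stands: this is a matter of efficiency.

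A reader might go further and infer that Bonferroni gives up power for nothing. The article does not support that. It plans confidence intervals, and Bonferroni extends directly to simultaneous intervals that agree with its tests, while Holm has no simple counterpart. The article does not say whether its intervals are meant to be simultaneous, so this benefit cannot be assumed away.

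A reader might also infer that the plan sets up one family of all outcomes at all four visits. The words do not say so. The sentence closes a description of contrasts within a mixed model and could mean the contrasts within each model. The family may properly be defined in the analysis plan, which is not shown. Holm's advantage holds for any family of more than one test, but its size does not carry over.

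Finally, the larger gains need every effect to be real and of equal size, and they need d of 0.5 or 0.65 where the article prints 0.25. That limit also stands, and for that reason the table shows the whole range.

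**Conclusion.** The point holds as an efficiency improvement. For tests on the same p-values, Holm keeps the same strong familywise control and never rejects less than Bonferroni. If all effects are real and equal, and d is 0.5 to 0.65, the gain in mean power is about 7 to 12 points with 11 tests and about 3 to 9 points with 44. It is about 1 to 3 points if roughly half are real, and under 1 point if only two are or if d is 0.25. These figures rest on 42 per arm, between-test correlation 0.4, a normal approximation and an assumed familywise level of 0.05.

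Two stronger conclusions do not follow. The planned error control is not faulty. Nor would Holm repair a sample size set at an unadjusted 0.05: it recovers part of the power lost to the correction and leaves the chance of at least one detection essentially as it was.

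**What to change.** Before unblinding, replace the reference to Bonferroni with *the Holm step-down procedure at familywise 0.05*, applied to the family that the plan defines, and report Holm-adjusted p-values. Bonferroni-adjusted or unadjusted confidence intervals can stay beside them if labelled as such.

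The cost is one phrase in the plan and one option in the software already named (the HOLM option of SAS PROC MULTTEST, applied to the unadjusted p-values). No extra participants, visits or data are needed. The small downside is that an interval may occasionally disagree with a Holm decision, and a sentence in the plan should say that the tests govern. If matching simultaneous intervals matter more to the investigators than the extra power, keeping Bonferroni is defensible, and the plan should then give that reason.
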